|                                                                                                                                                                     |    |
|---------------------------------------------------------------------------------------------------------------------------------------------------------------------|----|
| Wound infiltration with bupivacaine and adrenaline during cesarean delivery to reduce postoperative pain: a randomized controlled trial                      | 1  |
|                                                                                                                                                                     | 2  |
| Protocol number: 0151-17-EMC.                                                                                                                                | 3  |
| Date of submission to IRB: October 26, 2017                                                                                                                  | 4  |
| Date of IRB approval of the final protocol: December 25, 2017                                                                                                | 5  |
| Date of approval of the EMC chair (final approval): January 14, 2018                                                                                         | 6  |
|                                                                                                                                                                     | 7  |
| Hypothesis                                                                                                                                                   | 8  |
| Subcutaneous infiltration with bupivacaine and adrenaline before wound closure during cesarean section (CS) will reduce the intensity of postoperative pain.        | 9  |
|                                                                                                                                                                     | 10 |
| Objective                                                                                                                                                    | 11 |
| To examine the effect of single-shot wound infiltration with bupivacaine and adrenaline during CS on postoperative pain according to the visual analog scale (VAS). | 12 |
|                                                                                                                                                                     | 13 |
| Design                                                                                                                                                       | 14 |
| Randomized controlled trial                                                                                                                                         | 15 |
| Study population                                                                                                                                             | 16 |
| Term pregnant women scheduled for a planned CS under regional anesthesia.                                                                                           | 17 |
| Inclusion Criteria                                                                                                                                           | 18 |
| • Planned CD                                                                                                                                                        | 19 |
| • Pfannenstiel wound CD                                                                                                                                             | 20 |
| • Maternal age 18-60 years.                                                                                                                                         | 21 |
| • Planned spinal anesthesia                                                                                                                                         | 22 |
| Criteria for exclusion                                                                                                                                       | 23 |
| • Allergy to adrenaline or bupivacaine                                                                                                                              | 24 |
| • Maternal diseases: cardiac, liver and kidney diseases, hyperthyroidism, chronic hypertension and pre-gestational diabetes.                                        | 25 |
|                                                                                                                                                                     | 26 |
| • Multiple gestation                                                                                                                                                | 27 |
| • Antenatal diagnosis of major fetal malformations                                                                                                                  | 28 |
| • Antepartum fetal death.                                                                                                                                           | 29 |
| • Emergency CS.                                                                                                                                                     | 30 |
| Research plan                                                                                                                                                | 31 |

|                                                                                                                                                                                                                                                                                                                                                                                                                                                             |                                  |
|-------------------------------------------------------------------------------------------------------------------------------------------------------------------------------------------------------------------------------------------------------------------------------------------------------------------------------------------------------------------------------------------------------------------------------------------------------------|----------------------------------|
| Women will be recruited prior to the scheduled CS during the routine preoperative assessment.                                                                                                                                                                                                                                                                                                                                                               | 32
33                         |
| Consented women will be randomly assigned to the study (intervention) group or the control group.                                                                                                                                                                                                                                                                                                                                                           | 34
35                         |
| In the study group, the wound will be infiltrated in both sides with 30 ml of 0.25% bupivacaine hydrochloride mixed with adrenaline 1:200000 before wound closure.                                                                                                                                                                                                                                                                                          | 36
37                         |
| Infiltration will not be performed in the control group. Other intra- and postoperative management will be similar in both groups.                                                                                                                                                                                                                                                                                                                          | 38
39                         |
| On admission to the maternity ward, pain measurements will be recorded every 2 h for the first 6 h and then every 6 h until 24 h after admission, according to the ward protocol. Pain will be assessed by a VAS from 0 to 10, where a higher score indicates more pain.                                                                                                                                                                                    | 40
41
42                   |
| At 24 hours after surgery the women will be asked to grade their satisfaction regarding pain management after surgery on a scale of 1 to 5 where 1 = not satisfied and 5 = very satisfied.                                                                                                                                                                                                                                                                  | 43
44                         |
| Demographic and obstetric data will be collected from the computerized sheets: woman's age, weight and height, smoking status, pre-pregnancy weight, pregnancy and birth number, number of previous caesarean sections, gestational age, background diseases, obstetric complications, use of anticoagulants, reasons for surgery, duration of surgery, type of anesthesia in surgery, and administration of analgesia at the recovery and maternity wards. | 45
46
47
48
49
50 |
| Primary outcome                                                                                                                                                                                                                                                                                                                                                                                                                                      | 51                               |
| The primary outcome will be the mean VAS scores after admission to the maternity ward.                                                                                                                                                                                                                                                                                                                                                                      | 52                               |
| Secondary outcomes will include VAS score at each time point, need for rescue opioids, duration of surgery, time from end of surgery to mobility, time from end of surgery to breastfeeding, hematoma or infection in the surgical scar, maternal satisfaction, and length of stay after surgery.                                                                                                                                                           | 53
54
55
56
57       |
| Research period                                                                                                                                                                                                                                                                                                                                                                                                                                      | 58                               |
| Women will be recruited prior to the scheduled CD during the routine preoperative assessment and will participate in the study until they discharge home after the surgery.                                                                                                                                                                                                                                                                                 | 59
60                         |
| Randomization                                                                                                                                                                                                                                                                                                                                                                                                                                        | 61                               |
| Women will be randomly assigned to the study group or the control group at a 1:1 ratio. A computer-generated random allocation in blocks of ten will be created. The randomization list will be concealed in a closed study box. Eligible women will be assigned the next available sequence in the randomization list. Investigators and participants enrolled will be unaware of the upcoming group assignments until the moment of assignment.           | 62
63
64
65
66       |

|                                                                                                                                                                                                                                                                                                                                                                                                                                                                                                                    |                                  |
|--------------------------------------------------------------------------------------------------------------------------------------------------------------------------------------------------------------------------------------------------------------------------------------------------------------------------------------------------------------------------------------------------------------------------------------------------------------------------------------------------------------------|----------------------------------|
| Sample size                                                                                                                                                                                                                                                                                                                                                                                                                                                                                                 | 67                               |
| The standard deviation reported in the literature regarding post-cesarean VAS ranges from 0.1 to 2.7.* We assume a large amount of variation will exist within the groups, and therefore a standard deviation of 3.0 will be chosen. Based on this assumption and to demonstrate a difference of 1 in mean VAS score between the groups, 286 women (143 in each group) will be required with a power of 80% and a two-sided alpha of 5%. We are seeking approval to recruit up to 300 women in cases of a dropout. | 68
69
70
71
72
73 |
75
76
77             |
| Statistics                                                                                                                                                                                                                                                                                                                                                                                                                                                                                                  | 78                               |
| T-test will be used to examine differences in continuous variables between the groups. For the purpose of comparing the categorical research variables, Chi-square or the Fisher exact test for small samples we be used. Other statistical testes will be used as needed.                                                                                                                                                                                                                                         | 79
80
81                   |
| Maintaining confidentiality                                                                                                                                                                                                                                                                                                                                                                                                                                                                                 | 82                               |
| Patients' information will be stored separately in a sealed brown envelope and will not be included on the data collection sheet.                                                                                                                                                                                                                                                                                                                                                                                  | 83
84
85                   |
| Amendments related to trial protocol:                                                                                                                                                                                                                                                                                                                                                                                                                                                                       | 86                               |
| Date: 29.01.2018                                                                                                                                                                                                                                                                                                                                                                                                                                                                                            | 87                               |
| Addition to the exclusion criteria:                                                                                                                                                                                                                                                                                                                                                                                                                                                                                | 88                               |
| • Maternal cardiac disease                                                                                                                                                                                                                                                                                                                                                                                                                                                                                         | 89                               |
| • Chronic Hypertension                                                                                                                                                                                                                                                                                                                                                                                                                                                                                             | 90                               |
| • Hyperthyroidism                                                                                                                                                                                                                                                                                                                                                                                                                                                                                                  | 91                               |
| • Pre-gestational diabetes                                                                                                                                                                                                                                                                                                                                                                                                                                                                                         | 92
93
94
95
96
97 |

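### One randomization list in a closed box, with constant blocks of ten disclosed in the protocol, is not sufficient to keep upcoming assignments unknown in a trial without sham or described blinding

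*Protocol*

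**What the plan says.** The Randomization section of the protocol sets the ratio ("Women will be randomly assigned to the study group or the control group at a 1:1 ratio"), the block scheme and the means of concealment ("A computer-generated random allocation in blocks of ten will be created. The randomization list will be concealed in a closed study box"), and the way assignments are drawn ("Eligible women will be assigned the next available sequence in the randomization list"). It closes with an assertion: "Investigators and participants enrolled will be unaware of the upcoming group assignments until the moment of assignment".

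The Research plan section bears on this in two places. Consent comes before assignment: "Consented women will be randomly assigned to the study (intervention) group or the control group". The control arm has no sham: "Infiltration will not be performed in the control group". No blinding of anyone is described in the protocol.

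The protocol does not say who generates, holds or opens the list, whether its entries are covered one by one, or when in relation to surgery the assignment is drawn.

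**The concern.** The protocol makes a claim about concealment and also describes the means of achieving it, so the one can be tested against the other. There are two separate routes by which an upcoming assignment could become known.

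- **Seeing the list.** The concealed object is a sequential list, and the only barrier described is one closed box. The list must be consulted for each woman. Nothing described hides the entries below hers.
- **Counting within blocks.** A single block size is printed in the protocol, and treatment received is visible in theatre. Once five of ten places in a block have gone to one arm, the remaining places are determined.

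At stake is selection at the point where women are approached or asked for consent. A recruiter who knows or suspects the next arm can approach or defer a woman according to how much pain she is expected to have. The primary outcome is a self-reported VAS and the target difference is 1 point, so a systematic difference between the women entering each arm would feed directly into the comparison.

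**Working it through.** **Inputs.** Ratio 1:1 and block size 10 (Randomization); recruitment ceiling 300, required total 286, target difference 1 VAS point, SD 3.0 (Sample size).

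**The plan's own figure.** The protocol gives no figure for predictability. Its sample size, which is not in dispute, reproduces: a two-sided 5% t-test with 80% power, difference 1 and SD 3.0 needs 142.2 per arm, rounded up to 143, or 286 in total.

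**Route 1, the list.** No arithmetic is needed. If entries are uncovered and the person opening the box recruits, all remaining assignments can be known. If each entry is covered, or an independent person reads out one at a time, none is known by this route. The text does not say which applies.

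**Route 2, certain assignments.** A place is determined in advance when all five places of the other arm come before it. Among that place and those five, it is last with probability 1/6. Over the ten places:

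- expected determined places per block = 10 × 1/6 = 1.67, or 16.7%
- over 300 women, 30 blocks × 1.67 = 50; over 286 women, 286 × 0.1667 ≈ 48

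**Route 2, best guesses.** The strategy is to name the arm with more places left, and to toss a coin when they are equal.

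- expected correct guesses per block = 5 + (2^10 / C(10,5) − 1)/2
- = 5 + (1024/252 − 1)/2 = 5 + 1.53 = 6.53, or 65.3%
- over 300 women, about 196 correct, against 150 by chance

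Both are averages for a recruiter who knows the block size, the block boundaries and every earlier assignment.

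**Other block schemes, same measure.**

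| Scheme | Guessed correctly | Known with certainty |
|---|---|---|
| Fixed 4 | 70.8% | 33.3% |
| Fixed 6 | 68.3% | 25.0% |
| Fixed 10 (protocol) | 65.3% | 16.7% |
| Fixed 20 | 61.7% | 9.1% |
| Random 6/8/10 (simulated) | 66.4% | not computed |
| Random 4/6/8 (simulated) | 68.1% | not computed |

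The simulated rows use the running imbalance alone. Varying the size does not lower guessing accuracy, because small blocks also pull the arms back to balance. What it removes is certainty about where a block ends.

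**Illustration of bias, on an assumption not in the document.** Suppose recruiters enter women whose expected VAS differs by η points according to the guessed arm. With a proportion p of correct guesses, the bias is η(2p − 1).

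- Block guessing: 2 × 0.653 − 1 = 0.306, so η = 0.5 to 1.0 gives 0.15 to 0.31 point.
- List seen (p = 1): 0.5 to 1.0 point.

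These stand against a target difference of 1 point. The protocol offers no basis for choosing η.

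**The case against.** The strongest reply is that thin description is not failure. The protocol says that the list is concealed and that upcoming assignments are unknown. Covered entries or an independent holder are not described, but neither are they excluded. This stands: a reader might infer that concealment cannot work or has failed, and the text does not support that. It supports only that the stated mechanism is not enough to secure the stated claim.

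Four further points carry weight.

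- The 16.7% and 65.3% need a recruiter with complete knowledge. The protocol does not say who recruits or whether recruiters learn what was done in theatre. That the trial is open is itself an inference, though a fair one, from the absence of a sham and of any blinding statement.
- Ten is a fairly large block and less predictable than four or six. The single list is the more serious weakness.
- A reader might infer that no analysis could repair the damage. That goes too far: the Research plan collects number of previous cesareans, weight and height, so imbalance in these could be seen and adjusted for. Selection on unmeasured factors would remain.
- These are planned cesareans and consent precedes assignment, so steering would have to happen when women are approached or consent. That narrows the opportunity without closing it.

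The point cannot be left to a statistical analysis plan. Concealment is a matter of trial conduct, and this protocol fixes a mechanism for it.

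**Conclusion.** The concern holds in a limited form: the mechanism in the Randomization section does not by itself ensure what that section asserts. The exposure through the list depends on an unstated fact, namely whether entries are individually hidden from the person who opens the box. The exposure through block counting is at most 16.7% of assignments known with certainty on average (about 50 of 300) and 65.3% guessed correctly, both conditional on full knowledge of block size, boundaries and earlier assignments.

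No bias in the VAS comparison has been shown, and its size cannot be computed from the document. The point still deserves action, because following the plan as written leaves a route to selection in a trial with a self-reported outcome, and a better method is cheap.

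**What to change.** Amend the Randomization section as follows.

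- Release assignments one at a time, for example in sequentially numbered, opaque, sealed envelopes holding one assignment each and prepared by someone who does not recruit. Write the consented woman's identifier on the envelope before it is opened. An independent list holder who releases single entries would serve the same purpose.
- State who generates and who holds the list.
- Remove the block size from the document that recruiters hold. Preferably vary it at random, so that block ends cannot be known with certainty. This is an addition to one-at-a-time release and not a substitute for it, since it does not lower guessing accuracy.

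The cost is a regenerated list, about 300 envelopes and a one-paragraph amendment. The sample size does not change. Balance becomes looser only if some blocks exceed ten, since with blocks of ten or fewer the arms can never differ by more than the present maximum of five.

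### The protocol conceals the allocation only until assignment and describes no masking afterwards, so with a self-reported primary outcome and an untreated control, expectation cannot be separated from drug effect

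*Protocol*

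**What the plan says.** The Design section calls the study a randomized controlled trial and says nothing about blinding. The Randomization section says of the list, "The randomization list will be concealed in a closed study box", and of awareness, "Investigators and participants enrolled will be unaware of the upcoming group assignments until the moment of assignment". No other sentence in the protocol deals with who knows the arm.

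Under Research plan, the study group's wound is infiltrated with bupivacaine and adrenaline before closure. For the other group, "Infiltration will not be performed in the control group". No placebo or sham is described. The same section adds: "Other intra- and postoperative management will be similar in both groups".

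Pain is measured repeatedly on the maternity ward up to 24 hours after admission there: "Pain will be assessed by a VAS from 0 to 10, where a higher score indicates more pain". Satisfaction is asked for at 24 hours after surgery. Under Primary outcome: "The primary outcome will be the mean VAS scores after admission to the maternity ward". The secondary list begins: "Secondary outcomes will include VAS score at each time point, need for rescue opioids". It also contains maternal satisfaction.

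The Sample size section plans "to demonstrate a difference of 1 in mean VAS score between the groups".

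**The concern.** Concealing the list keeps the recruiter from foreseeing the next allocation, so it guards against selection bias. It does nothing for the measurement of outcomes after allocation. Here the primary outcome is a rating the woman gives herself, satisfaction is another, and the need for rescue opioids depends on her request and on judgement at the bedside. The protocol's hypothesis is directional: infiltration is expected to lower pain. A woman who knows that she did or did not receive local anaesthetic may rate her pain in line with that expectation, and someone who knows her arm may record it so.

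At stake is what the primary comparison means. A difference in mean VAS would combine any drug effect with any effect of knowing the treatment, and no later analysis can pull them apart. A larger sample does not help: it makes a given bias easier to declare significant. Who is masked, and until when, has to be settled before the first operation, so this cannot be left to an analysis plan.

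**Working it through.** **Inputs.** From the Sample size section: difference 1 VAS point, SD 3.0, two-sided alpha 5%, power 80%, 143 women per group, and a literature SD range of 0.1 to 2.7. From the Statistics section: t-test. The size b of an expectation or reporting effect is not in the protocol, so 0.3 and 0.5 point are assumed here, with larger values shown for scale.

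**1. The plan's own figure.** The normal approximation is n = 2(1.960 + 0.842)² × 3.0² / 1² = 141.3, rounded up to 142 per group. The t-based solution is 142.25, rounded up to 143 per group and 286 in all. The stated sample size reproduces, and this point does not alter it.

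**2. Standard error.** SE = SD × √(2/143) = SD × 0.11826.
- SD 3.0: SE = 0.3548
- SD 2.7: SE = 0.3193

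**3. Smallest observed difference that reaches p<0.05.** The t critical value on 284 df is 1.968.
- SD 3.0: 1.968 × 0.3548 = 0.70 point
- SD 2.7: 1.968 × 0.3193 = 0.63 point

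**4. Chance of p<0.05 with no drug effect and a bias of b.** This is P(|T| > 1.968), where T is noncentral t on 284 df with noncentrality b/SE. For b = 0.3 at SD 3.0, for example, the noncentrality is 0.3/0.3548 = 0.846.

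| Assumed bias b | SD 3.0 (planned) | SD 2.7 (top of cited range) |
|---|---|---|
| 0 | 5.0% | 5.0% |
| 0.3 | 13.4% | 15.5% |
| 0.5 | 29.0% | 34.5% |
| 0.75 | 55.8% | 64.8% |
| 1.0 | 80.2% | 87.7% |

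The normal approximation moves the 0.3 and 0.5 rows by at most 0.2 percentage points. A smaller SD raises the figures further: at SD 2.0, which is inside the cited range but is not a planning value, they are 24.4% for b = 0.3 and 55.8% for b = 0.5.

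**5. Direction.** The table treats b as a net shift in favour of infiltration. Expectation would plausibly act that way. Rescue may not: if controls are given rescue more readily because they are known to have had no infiltration, their VAS falls and the observed difference shrinks. The net direction cannot be derived from the protocol.

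**The case against.** The strongest reply is that the quoted sentence is a correct statement of allocation concealment, and that the fault is silence about what follows. That stands, and it rules out some stronger readings that a reader might infer:

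- **That women are told their arm, or that ward staff know it.** The protocol says neither. The sentence names investigators and enrolled participants, and ward staff do not appear in it. Infiltration takes place before wound closure, and spinal anaesthesia is planned, so some women may never learn their arm. In that case the bias could be small. But nothing in the protocol secures this.
- **That expectation alone would produce the difference sought.** The target is 1 point, so a bias of a full point would be needed to produce all of it. The assumed biases of 0.3 and 0.5 show a raised false-positive rate, which is a different claim.
- **That the bias almost certainly favours infiltration.** Unequal rescue could work against it, as shown above.

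It is also fair to say that the percentages rest on assumed biases. They show how sensitive the design is and do not estimate what will happen.

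What remains after these objections is enough: a self-rated primary outcome, an untreated control without sham, and no provision for masking once the arm is assigned.

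**Conclusion.** The point holds as a gap in the design. As written, the protocol gives no means of separating an expectation or reporting effect on VAS from a drug effect, and satisfaction and rescue opioids are exposed in the same way.

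Its size depends on an unknown. For a net bias of 0.3 to 0.5 point towards infiltration and no drug effect, the false-positive rate would be 13.4% to 29.0% at SD 3.0 and 15.5% to 34.5% at SD 2.7, in place of 5%. These figures assume 143 analysed women per group, a two-sided t-test on mean VAS, and a constant shift between groups. The conclusion that the two effects cannot be separated needs none of these assumptions.

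**What to change.** Keep the concealment sentence, which is valid and still needed, and add text after it along these lines:

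- Women, and the staff who record VAS and collect the satisfaction score, are not told the arm until both the 24-hour VAS and the satisfaction score have been recorded. The two 24-hour clocks differ (ward admission for VAS, surgery for satisfaction), so masking should last until the later of the two.
- The arm is kept out of ward-visible study notes as far as feasible, and is available at once to treating clinicians whenever care requires it.
- At 24 hours, after those scores and before any disclosure, each woman is asked to guess her arm. The guesses are reported by group.

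If this is not feasible, the protocol should state that the trial is open-label and limit the conclusion to infiltration given with knowledge of treatment compared with none.

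**Cost.** Protocol wording, a charting instruction, one extra question per woman, and a restricted arm record with an access route. No extra participants are needed. The protocol draws data from computerized sheets, so the arm may also be visible in routine records, and the charting step may take more work than the wording suggests. Without a sham, masking of an awake patient may be imperfect. The guess question gives an indication of how far it failed.
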